All interventions will be carried out by burns clinicians with extensive experience in the application of dressings and NPWT. Following their initial presentation, participants will return to the OPD 3 to 5 days later for a change of dressings and, for those in the intervention group, a replacement of their NPWT system. To alleviate any additional pain from the removal of the adhesive drape, the clinicians replacing the NPWT apparatus will apply Niltac™ (ConvaTec, Greenlane, NZ), a silicone-based spray that can effectively dissolve the film and ease extraction. Participants will continue to present to the burns clinic every 3 to 5 days for dressing and NPWT changes until the wound is fully re-epithelialised or until grafting is required.

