#### Blinding

The nature of the interventions precludes full blinding, but a number of key assessments will be blinded to minimise performance bias. By necessity, treating clinicians will be aware of group allocation throughout the duration of the participants’ care until the point of healing. Clinical judgements of re-epithelialisation, therefore, will not be blinded, but the use of 3D photographs will allow for a later review by a panel of blinded assessors. These assessors will not be provided any details pertaining to the participants’ management. If there any discrepancies, the blinded measures (or the majority thereof) will supersede those taken by clinicians.

Skin and scar assessments performed at 3- and 6-month follow-up appointments will also be blinded, as the clinical evaluators will have no knowledge of participants’ acute care. To reduce the risk of performance bias further, ultrasound images taken at these follow-ups will be reviewed by blinded assessors, who will measure scar and wound site thicknesses.

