#### Primary outcome measure

##### Time to re-epithelialisation

The primary outcome will be time to full re-epithelialisation, as measured by the number of days from the injury to 95% re-epithelialisation of the burn wound. Percentage re-epithelialisation will be assessed at every clinical visit using multiple methods. A treating consultant will first perform an examination and record their assessment. Digital 3D photographs will then be taken of the burn using the 3DLife Viz II (Quantificare, Valbonne, France) and the D400 3D (Intel, Santa Clara, US) cameras. These photographs will be analysed using the software programs DermaPix (Quantificare, Valbonne, France) and 3D WoundCare (GPC, Swansea, UK), respectively, and undergo blinded review by a panel of three burns clinicians.

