#### Data analysis

Conventional descriptive statistics will be used to describe the characteristics of the sample.

The potential effect of time to treatment, burn depth, burn TBSA, mechanism of injury, anatomical location of the burn and skin type will also be tested against primary and secondary measures in univariate analyses. Variables with *p*
< 0.1 will be included as covariates in the primary and secondary analyses. Sensitivity analyses will also be conducted without adjustment for covariates.

Generalised linear (mixed) models will be prepared to examine primary and secondary outcomes across time and between groups, with patients as random effect where analyses include repeated measures within a patient. If mixed models do not converge with patient as a random effect, robust variance estimates for cluster-correlated data will be used [128]. For outcomes with repeated measures, the fixed effects of time, group and interaction time by group will be tested. Data will be analysed as intention-to-treat (primary analysis) and on a per protocol basis (sensitivity analysis) if deviations from the protocol occur. Missing data will be handled using multiple imputation where appropriate. Significance will be set at 0.05. Statistical analyses will be performed using Stata (StataCorp LLC College Station, TX:) or SPSS (IBM Corp, Armonk, NY, USA).

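### Healing is known only to within a 3-to-5-day visit gap; the analysis as stated does not use those bounds, and the blinded override protects mainly in one direction

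*Protocol article*

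**What the plan says.** All references are to the protocol article.

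- **Endpoint** (Time to re-epithelialisation): a single day count, "as measured by the number of days from the injury to 95% re-epithelialisation of the burn wound".
- **When it is seen** (same section): "Percentage re-epithelialisation will be assessed at every clinical visit using multiple methods".
- **Visit schedule** (Interventions): after the first dressing change, attendance is set at "every 3 to 5 days for dressing and NPWT changes until the wound is fully re-epithelialised". A graft also ends these visits. The wording is the same for both arms.
- **Who judges healing** (Blinding): the clinicians' own call is unblinded, and 3D photographs are read afterwards by people unaware of the allocation. The photographs "undergo blinded review by a panel of three burns clinicians" (Time to re-epithelialisation), and where readings differ "the blinded measures (or the majority thereof) will supersede those taken by clinicians".
- **Missing photographs** (Discussion): 3D photography will sometimes be impossible, and the consultant's judgement is offered for that case.
- **Analysis** (Data analysis): "Generalised linear (mixed) models will be prepared to examine primary and secondary outcomes across time and between groups". Multiple imputation is named for missing data, where appropriate. No censoring method is named, and no rule says how a healing day between two visits is dated.

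**The concern.** There are two separate problems.

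**Bounds that are not used.** The true 95% date lies after the last visit below 95% and no later than the first visit at or above it. That gap is 3 to 5 days, about the size of the 3.4-day target effect. If the first healed visit is taken as the day of healing, the date is late by about half a gap on average. This cancels between arms only if the gaps are alike. Staff who know the allocation book the visits, within a permitted range of 3 to 5 days. A child who stops attending unhealed also carries information, because healing came after the last visit. A model for a day count with imputation does not, as stated, use that bound.

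**A one-way safeguard.** Visits run until healing, and during the acute phase it is the unblinded clinician who judges this. The panel reads the photographs later. If the clinician called healing too late, the panel can choose an earlier photograph. If the clinician called it too early and visits stopped, the panel can disagree but has no later acute-phase photograph from which to date healing. Early calls favouring NPWT are the bias that blinding most needs to remove.

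**Working it through.** **1. The plan's own figure.** Inputs from Sample size: control mean 12.4 days, SD 5.4, difference 3.4, significance level 0.05 (two-sided assumed), power above 80%, drop-out up to 20%. The normal formula gives 2 × (1.960 + 0.842)² × 5.4² / 3.4² = 39.6, so 40 per arm. The exact t-test needs 41 per arm (power 80.4%). Then 41 / 0.80 = 51.25, rounded up to 52 per arm, or 104 in total. The stated number is reproduced, and the calculation treats healing time as a continuous day count compared by means.

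**2. Lateness from visit gaps.** If healing falls at random within gaps of length g, the recorded date is late on average by E[g²] / (2E[g]).
- Fixed gaps of 5 and 3 days: 2.5 − 1.5 = 1.0 day, or 1.0 / 3.4 = 29% of the target.
- Control gaps of 3/4/5 days in proportions 0.1/0.2/0.7: 21.6 / 9.2 = 2.35 days. NPWT in proportions 0.7/0.2/0.1: 12.0 / 6.8 = 1.76 days. The difference is 0.58 day.

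**3. Effect of early calls.** A call one visit too early moves the date back by one whole gap, on average E[g²] / E[g]. With gaps of 3, 4 and 5 days equally likely this is 50 / 12 = 4.17 days. Early calls in 10%, 20% and 30% of NPWT children therefore give 0.42, 0.83 and 1.25 days.

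**4. Simulation with no true effect.** Gamma healing times (mean 12.4, SD 5.4), first visit on day 0–2, t-test on the first healed visit, 41 per arm. The distribution, first-visit day, spacing mixes and early-call rates are assumptions.

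| Scenario | Control minus NPWT (days) | False positives |
|---|---|---|
| Same 3/4/5-day mix in both arms | 0.0 | 5.2% |
| Control mostly 5, NPWT mostly 3 | 0.57 | 7.4% |
| Control 5, NPWT 3 | 0.97 | 12.8% |
| Control 3, NPWT 5 | −1.0 | 13.8% |
| Same mix, 10% uncorrected early NPWT calls | 0.43 | 6.2% |
| Same mix, 20% | 0.84 | 10.2% |
| Same mix, 30% | 1.26 | 17.2% |

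The simulated biases agree with steps 2 and 3. The false-positive rates can be checked by hand: the standard error is 5.55 × √(2/41) = 1.23, 0.97 / 1.23 = 0.79, and Φ(−1.96 + 0.79) + Φ(−1.96 − 0.79) is about 12%.

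**5. With a true 3.4-day effect.** Equal spacing gives an estimate of 3.39 days and 77% power, against 79% with exact dates. Control at 3 days and NPWT at 5 gives 2.4 days and 51% power. Control at 5 and NPWT at 3 gives 4.4 days.

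**6. Using the bounds.** At the 5 v 3 day extreme with no true effect (42 per arm), a lognormal interval-censored model gave about 0 bias and 4% false positives, where the t-test gave 13%. With equal 4-day visits and healing times scaled by 9.0/12.4, power was 91% for that model and 88% for the t-test. A second set of runs put the two within two points (88% and 90%). These powers exceed those in step 5 because a ratio effect also shrinks the spread in the NPWT arm.

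**7. Children lost unhealed.** Planned drop-out is at most 20%, or 0.20 × 104 ≈ 21 children. That is a ceiling on how many could be right-censored, not an estimate.

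**The case against.** **The schedule is common to both arms.** This stands. A reader might infer that visit timing in itself creates a treatment effect. It does not: with equal spacing the bias is zero and the cost is about 2 points of power. The 1-day figure needs every child in one arm at 5 days and every child in the other at 3, which nothing in the article plans. Nor is the direction settled. The Discussion cites literature that NPWT lowers the frequency of procedures, and longer NPWT gaps would bias against NPWT.

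**The blinded majority overrides the clinician.** This stands in part. A reader might infer that clinician optimism simply becomes the endpoint, but the override rules that out as a general statement. If the panel corrected three quarters of a 20% early-call rate, the remaining 5% would give only 0.22 day and 5.7% false positives. However, correcting an early call to its true date needs a later photograph, and none would exist once visits had stopped. The article does not say how such a reading is coded.

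**The article does not say that days are treated as exact.** This also stands. It is a natural reading of a day-count endpoint with the named models, but generalised linear models include the discrete-time complementary log-log model, which handles intervals properly. An analysis plan that is not shown may specify it. The supportable statement is that the analysis as stated does not use the bounds.

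**Simple right-censoring at the last photograph is no cure.** This stands. Children called healed are close to healing, so censoring them is informative. With 20% early NPWT calls, all detected by the panel and then censored, simulation gave 10–11% false positives and a spurious 6–7% slowing of NPWT.

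**Conclusion.** The concern holds in a limited form. Healing dates are interval-censored, children lost unhealed are right-censored, and the analysis as stated uses neither fact. Under equal visit spacing this is harmless. If spacing differs by arm, the bias is up to about 1 day in either direction (about 30% of the target) with 13–14% false positives. For partial differences it is smaller, 0.57 day and 7.4% in the case worked. An interval-censored model removes this bias with essentially no loss of power.

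The blinded override guards well against late calls and poorly against premature ones. Uncorrected early calls in 10–30% of NPWT children would give about 0.4–1.3 spurious days and 6–17% false positives. That range is assumed; the article gives no disagreement rate. That visits stop on the clinician's call is inferred from the Interventions and Blinding sections together. The sizes also rest on gamma healing times with the article's mean and SD.

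**What to change.** 1. Record each child's outcome as the interval from the last visit below 95% to the first visit at or above 95%. Use the panel majority where photographs exist and the consultant's reading where none could be taken.
2. Analyse it with an interval-censored or discrete-time (for example complementary log-log) model, as the primary analysis or at least as a pre-specified sensitivity analysis. Right-censor children lost unhealed at their last visit.
3. Where the panel reads the last photograph as below 95% after a clinician's call of healed, do not treat this as ordinary non-informative censoring. Analyse once with the clinician's date and once as censored, and report both as bounds.
4. State separately how grafted children enter the analysis, for example with grafting as a competing event. A plain Weibull or lognormal model assumes that everyone eventually heals.
5. Report visit gaps and panel–clinician disagreements by arm.

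The cost is analysis wording and a little more work, since visit dates and panel readings are already to be collected. A parametric model adds a distributional assumption that must be checked.

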## Discussion

Over the past two decades, NPWT has been extensively applied and studied in the management of a wide variety of wounds, even prompting some authors to remark that it has “overwhelmed the wound-healing world” [129]. It is all the more surprising, then, that so little research has been conducted investigating the efficacy of the technique in the acute management of burns. In the limited volume of literature that does exist, there is promising evidence to suggest NPWT may reduce ischaemia, oedema formation and wound progression [49, 89–91]. However, the constraints of the animal model studies, case reports and retrospective studies that comprise the bulk of this literature cast substantial doubt on the applicability of their findings. To date, no results from appropriately powered RCTs with patient-centred outcomes have been published comparing NPWT to standard acute burns management [95, 130].

Furthermore, the underrepresentation of children in the NPWT literature (across all wound types, but in the context of acute burns particularly) overlooks a large segment of the burns patient population [5]. Children also tend to suffer disproportionately from some of the immediate and long-term risks that NPWT is believed to alleviate. It is believed that infants might be more sensitive to pain than adults [131], and the potential harms of hypertrophic scarring are far greater in patients still undergoing physical, social and psychological development [24].

Any attempts to extrapolate findings from the existing adult studies to a paediatric setting must be met with caution, not only due to the small sample sizes and methodological limitations of these trials, but also because young children differ markedly from adults in skin thickness and composition [132, 133], body surface area [134], and formation rates of granulation tissue [135]. The reluctance to employ NPWT in paediatric populations appears to stem from concerns about possible side effects, including bleeding, ischaemia and elevated pain [93]. However, reports of adverse events are rare in the literature, and the technique is widely regarded as safe when applied and monitored as per device instructions [136]. NPWT is known to cause pain at pressures greater than 125 mmHg [137], but this is well above the standard range preferred by the participating hospital. Anecdotally, the highest levels of pain experienced by paediatric patients undergoing NPWT are reported during removal of the adhesive film required to maintain the airtight seal. It is anticipated that with the application of Niltac™ prior to extraction, removing and re-applying the NPWT system will be no more painful than regular dressing changes. The overall risks of NPWT are, therefore, minimal, with most research focusing on the use of the therapy in children indicating that it is especially suited for paediatrics, as it reduces the frequency of procedures and allows for greater mobility than some standard dressings [138].

The trial was deliberately designed to serve as a pragmatic study of the efficacy of NPWT in the treatment of the broad spectrum of thermal burn injuries that routinely present to the participating ED and OPD. Especially for the latter, the burns seen over the course of even a single day tend to vary significantly in terms of first aid, prior treatment and time to presentation. For this reason, investigators have set a sample size that is large enough to account for the wide variability and allow for a statistical comparison of different groups.

The 7-day window for time to presentation was selected as it captures the majority of the OPD patient population. Although Morykwas et al*.* [89] found that NPWT was effective in their animal model only if administered within 12 h post-burn, there are strong reasons to believe that NPWT could continue to be of benefit to humans past this point. First and foremost are the pathophysiological differences between humans and animals, including the finding that the peak in post-burn oedema volume appears to occur later in humans than in non-human subjects [139–142]. Furthermore, multiple human studies have reported progression of burn surface area and depth over 4 to 5 days following injury [47], and high-protein oedema is known to remain in the interstitium for at least the first 7 days post-burn [139].

The range of assessments to be employed in this trial were selected for their reliability as well as the feasibility with which they could be carried out on paediatric patients. It is acknowledged that the age, size or distress of a patient may sometimes preclude researchers from completing certain assessments, such as 3D photography and LDI. To account for this potential limitation, additional measures of burn size, re-epithelialisation and depth will also be provided via the consultants’ clinical judgement.

### Study significance

Following a pilot study that yielded promising results, this trial aims to investigate the efficacy of NPWT in the treatment of acute paediatric burn injuries. By measuring the impact of NPWT on re-epithelialisation, burn wound progression and pain, the study aims to address the gaps in the NPWT literature and determine whether the therapy warrants implementation as an adjunct to standard therapy.

### Trial status

This manuscript represents the 15th version of the trial protocol, completed on 15 January 2019. Recruitment commenced on 2 May 2018 and is expected to conclude by 31 January 2019. At the time of writing, 103 participants have been recruited.

## Abbreviations

BBSIP: Brisbane Burn Scar Impact Profile
B/w: Between
DC: Dressing change
ED: Emergency department
FLACC: Face, Legs, Activity, Cry, Consolability
FPS-R: Faces Pain Scale, Revised
LDI: Laser Doppler imaging
NPWT: Negative pressure wound therapy
NRS: Numerical rating scale
OPD: Outpatient department
POH: Point of healing
POSAS: Patient and Observer Scar Assessment Scale
RCT: Randomised controlled trial
SMS: Short Message Service
SWATH: Sequential window acquisition of all theoretical fragment-ion spectra
TBSA: Total body surface area
